| Trial period:        | Q3 2021 – Q4 2023                                                                                                                                                                                                                                                                                                                                                                                                                                                                                                                                                                                                                                                                                                                                                                                                                                                                                                                                                                                                                                                                                                  |
| Statistical analyses | 
The analysis of the primary endpoint will be conducted on the Full Analys Set (FAS) and the Per Protocol Set (PPS).
 
The primary analysis of the primary endpoints will be performed using the ANCOVA, including randomisation strata of gender and disease severity together with treatment as fixed factors in the model.
 
The two primary endpoints will be adequately adjusted for multiplicity. The p-value for testing the null hypotheses, no difference between treatment groups, must be less than 0.05 to be considered to have met the primary objective.
                                                                                                                                                                                                                                                                                                                                                                                                                                                                                                                            |

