### 4.3 Primary endpoint:

Mean change from baseline to 13 weeks in RAND 36 domains role limitations due to physical health (RP) and physical functioning (PF).

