## 9.2 Statistical analyses

### 9.2.1 Sample size calculations

The assessment of the primary endpoints in this trial are based on the RAND 36-item health survey at baseline and 3 months where the domains of physical functioning and role functioning/physical defines the primary endpoints.

The primary endpoints have been used for long COVID (Garratt et al., 2021). There are norm data available for Sweden which enable us to determine a threshold for normalisation of individual RAND 36 domain levels. Using data from a few studies with similar methodology where RAND 36 has been previously used, we have assumed the standard deviation (SD) of Role Physical (RP), Physical Functioning (PF) 15.0. We expect the quality of life to be generally low in our cohort, especially in the RAND 36 RP and PF domains. We consider a ten points higher RAND 36 score in the HBO group compared to the placebo group to constitute a clinically relevant difference to be detected. Sample size calculation using t-test for independent groups, with 80% power, assuming a common SD of 15, and with a 5% significance level, reveals that at least 37 subjects per group are needed. We aim to recruit 80 subjects. An interim analysis will be made after 20 have undergone visit 2 to evaluate safety and when 40 subjects have undergone visit 3 in order to stop for futility and adjustment of sample-size if needed.

Sample size calculation was done in nQuery version 7.

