## 9.2.3 Patient Demographic and Baseline Characteristics

Baseline values and patient characteristics will be presented in tables by group and in total. All continuous variables will be described using standard statistical measures, i.e., number of observations, mean and median value, standard deviation, minimum and maximum value. All categorical variables will be summarised in frequency tables.

In general, continuous outcome variables will be analysed using ANCOVA, unless otherwise specified. Estimates will be presented using least square means for differences between treatment arms. For continuous endpoints that are measured repeatedly over time, such as EQ5D, RAND-36 domains, the change from baseline will be analyzed using a linear mixed effect model including baseline, treatment group, sex, symptom severity, visit, and treatment

|             |                |
|-------------|----------------|
| Trial Code: | HOT-LOCO       |
| Version No: | v.4            |
| Date:       | 2022-01-03     |
| EudraCT No: | 2021-000764-30 |

group by visit interaction, and subjects as random effects, in the models. An unstructured covariance matrix will be assumed.

Analysis for categorical data in terms of binary data (Yes/No) will be presented as the proportion of participants with the frequency of presence or absence by treatment group of the characteristics of interest and analysed using the CMH Chi-square test, where the parameter used for the statistical hypothesis testing will be the OR, as a measure of the relative difference in odds between treatment arms. An  $OR > 1$  indicates an efficacy in favour of HBOT compared to placebo.

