#### 9.2.4 Primary Endpoint Analysis

The analysis of the primary endpoint will be conducted on the Full Analys Set (FAS) and the Per Protocol Set (PPS).

The primary analysis of the primary endpoints will be performed using the ANCOVA, including randomisation strata of main symptom and gender together with treatment as fixed factors in the model.

The two primary endpoints will be adequately adjusted for multiplicity. The p-value for testing the null hypotheses, no difference between treatment groups, must be less than 0.05 to be considered to have met the primary objective.

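### Neither statement of the primary ANCOVA of change names the baseline RP or PF score as a covariate, which gives away some precision at no saving

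*Protocol*

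**What the plan says.** Section 4.3 defines the primary endpoint as "Mean change from baseline to 13 weeks in RAND 36 domains role limitations due to physical health (RP) and physical functioning (PF"). RAND-36 is completed at visit 1 (Table 1) and also serves as an eligibility test (section 6.2), so every randomised subject should have a baseline score.

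The primary model is described twice, and the descriptions differ:

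- Synopsis, Statistical analyses: ANCOVA "including randomisation strata of gender and disease severity together with treatment as fixed factors in the model".
- Section 9.2.4: the same method, but this time "including randomisation strata of main symptom and gender together with treatment as fixed factors in the model".

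Section 9.2.3 gives a further model for continuous outcomes assessed at several visits, with EQ-5D and the RAND-36 domains as its examples. Change in these is "analyzed using a linear mixed effect model including baseline, treatment group, sex, symptom severity, visit", among other terms. Baseline is an explicit term there.

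Section 7.5 stratifies randomisation by RAND-36 disease severity and gender. It does not mention main symptom.

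**The concern.** The protocol does not stay silent on model terms. It lists them for the primary analysis, and both lists hold only treatment and two categorical factors. For a mixed model of change in RAND-36 domains it names baseline; for the primary ANCOVA of change in two of those same domains it does not. Taken at its word, the primary model has no continuous covariate.

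A change score carries the noise of the baseline measurement. Regressing on baseline removes that noise and any chance imbalance in baseline between two groups of 40. What is at stake is the width of the confidence interval and the power for each domain. How much is lost depends on whether the model already carries RAND-36 severity, and the two descriptions disagree on exactly that.

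**Working it through.** **Inputs from the protocol.** Difference 10 points, SD 15, two-sided 5%, 80% power (sections 9.2.1 and 9.2.2.2); 80 subjects at 1:1, so 40 per group; eligible baseline scores at most 70 (section 6.2); severity bands below 30, 30–50 and above 50, which are listed as subgroups in section 9.2.2.3. The cut-offs used for stratification are not given.

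**Assumptions.** The correlation r between baseline and week 13 is not stated; 0.3, 0.5 and 0.7 are used. Variances are taken as equal at the two visits. Section 9.2.1 does not say whether 15 is the SD of the score or of the change, so both are shown.

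**Step 1: the plan's own figure.** Exact noncentral-t power for a two-sample t-test is 0.797 with 36 per group and 0.808 with 37. The stated 37 is reproduced. With 40 per group, power is 0.838.

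**Step 2: baseline covariate against no baseline information.**

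- Variance of change: 2·SD²·(1 − r)
- Variance adjusted for baseline: SD²·(1 − r²)
- Ratio: (1 + r)/2, so the reduction is (1 − r)/2, which is 35%, 25% and 15% at r = 0.3, 0.5 and 0.7

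If 15 is the SD of the score, 40 per group:

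| r | SD of change, 15·√(2(1 − r)) | Power | Adjusted SD, 15·√(1 − r²) | Power |
|---|---|---|---|---|
| 0.3 | 17.75 | 0.701 | 14.31 | 0.870 |
| 0.5 | 15.00 | 0.838 | 12.99 | 0.925 |
| 0.7 | 11.62 | 0.967 | 10.71 | 0.985 |

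If 15 is the SD of change, the adjusted SD is 15·√((1 + r)/2) = 12.09, 12.99 and 13.83, and power rises from 0.838 to 0.955, 0.925 and 0.891.

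This comparison is close to the 9.2.4 wording, unless main symptom tracks the baseline score.

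**Step 3: baseline covariate against a model that already has severity bands.** This is the relevant comparison for the synopsis wording. Baseline was simulated as a normal score truncated to 0–70 (means 30 to 45, SD 15 or 20 before truncation). The strata were taken to be the 9.2.2.3 bands of the analysed domain. The ratio of covariate-adjusted to band-adjusted variance was:

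- r = 0.3: 0.893 to 0.925
- r = 0.5: 0.931 to 0.952
- r = 0.7: 0.962 to 0.974

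The further cut is therefore about 3% to 11%. Dividing the adjusted SD by the square root of these ratios gives the band-model SD. With score SD 15 and 40 per group:

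| r | SD with bands | Power with bands | Power with baseline |
|---|---|---|---|
| 0.3 | 14.31/√0.893 = 15.14 to 14.31/√0.925 = 14.88 | 0.83–0.84 | 0.870 |
| 0.5 | 12.99/√0.931 = 13.46 to 12.99/√0.952 = 13.31 | 0.91 | 0.925 |
| 0.7 | 10.71/√0.962 = 10.92 to 10.71/√0.974 = 10.85 | 0.98 | 0.985 |

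**Step 4: RP separately.** RP has four items, so with all four answered the eligible values are 0, 25 and 50. Bands then merge 0 with 25. Over four assumed distributions of these values the ratio ran from 0.809 to 0.957, a further cut of about 4% to 19%.

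**The case against.** The strongest reply is that the sentence lists fixed factors, and a continuous baseline score is not a fixed factor. Its absence from that list need not exclude it. The method is called analysis of covariance, section 9.1 calls the section a summary, and a separate SAP will give the technical detail. Section 9.2.3 already adjusts RAND-36 domains for baseline and does not confine that model to secondary endpoints. This has weight: a reader might infer that the sponsor rejected baseline adjustment and will run a plain ANOVA of change, and the documents do not support that. What remains is that no covariate is stated for the primary model, whereas one is stated for the other.

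A second reply concerns size. The synopsis model contains disease severity, which section 7.5 ties to RAND-36. If that factor is the banded score of the analysed domain, most of the gain is already captured. This also stands, and it rules out quoting the 0.701 against 0.870 contrast as the loss under the synopsis wording. It is less secure than it looks: the stratum cut-offs are not stated, the bands in section 9.2.2.3 refer to RP and PF jointly, and one severity factor need not represent both domain baselines well.

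Third, a reader might infer that the trial was sized on the wrong variance. The SD of 15 is not labelled as belonging to the score or the change, so that cannot be shown.

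**Conclusion.** The point holds as a cost-free improvement in precision. Both descriptions of the primary ANCOVA leave out the baseline score of a change-from-baseline endpoint, and they disagree on which strata are in the model. Because allocation is randomised, there is no bias and no inflation of the type I error, and the 37 per group stands.

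The size depends on which description is followed. Under 9.2.4 the variance given away is near 35% to 15% for r from 0.3 to 0.7, unless main symptom tracks baseline. Under the synopsis, with score SD 15, the gain in power from adding baseline is about 3 to 4 percentage points at r = 0.3, 1 to 2 at r = 0.5, and under half a point at r = 0.7. These figures rest on assumed correlations, equal variances at both visits, and strata equal to the 9.2.2.3 bands of the analysed domain on a continuous score. For RP the bands are coarser and the remaining gain is somewhat larger.

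**What to change.** In the synopsis and in section 9.2.4, use the same text: *ANCOVA of change, for RP and PF separately, with treatment and the randomisation strata actually used (gender and RAND-36 disease severity, section 7.5) as fixed factors, and the continuous baseline score of the same domain as covariate.* This replaces main symptom in 9.2.4, so that both statements agree with section 7.5. It would help to add a sentence saying how the 9.2.3 mixed model relates to this primary ANCOVA, since both cover RAND-36 domains.

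The cost is one phrase in two places, carried through to the SAP before database lock. The baseline scores are already collected at visit 1, so no extra data, visits or subjects are needed.

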## 2. Introduction

### 2.1 Background

Post COVID-19 Syndrome (PCS), Post Acute COVID-19 Syndrome (PACS) or Long COVID Syndrome (Long COVID) has been defined as 'signs and symptoms that develop during or following an infection consistent with COVID-19, continue for more than 12 weeks and are not explained by an alternative diagnosis' (Venkatesan, 2021).

Common symptoms are fatigue, post-exertional malaise, brain fog, neurologic sensation, headaches, memory issues, insomnia, muscle aches palpitations, shortness of breath, dizziness and speech issues. Nearly 50% have reduced working capability and 22% cannot work at all. A majority are women and have never been hospitalized for acute COVID-19 (Davis et al., 2020).

The most common organ affected by the SARS-CoV-2 virus is the lung due to its main site of entry, binding to the angiotensin-converting enzyme 2 (ACE-2) receptor; resulting in damage to the cells of the alveolar-capillary membrane (Bourgonje et al., 2020). COVID-19 is associated with endothelial dysfunction, tissue edema and a pro-coagulant state in various organs including the lungs, liver, heart, kidney and small bowel (Varga et al., 2020).

Many of these changes may become chronic, which have been observed at post-COVID follow up (Halpin et al., 2021). COVID-19 should not only be viewed upon as an acute infection but as an inductor of a chronic inflammatory disease. Chronic oxidative stress, inflammation and endothelial dysfunction may explain many of the symptoms and objective findings associated with post-acute and long COVID even after recovery from the viral infection (Chang et al., 2020). These features are also hallmarks of other post-viral syndromes such as Myalgic Encephalomyelitis/Chronic Fatigue Syndrome (ME/CFS)(Scherbakov et al., 2020)

Endothelial dysfunction is a potentially reversible condition that serves as an independent predictor of cardiovascular events(Bonetti et al., 2003). Reactive Hyperemia Pulse Amplitude Tonometry (RH-PAT) is a non-invasive, user-independent tool for assessment of endothelial dysfunction. RH-PAT can be used in a clinical setting for monitoring of treatment effect in subjects with this condition (Bonetti et al., 2004). Autonomic dysfunction is an early marker of endothelial damage and is associated with cardiovascular morbidity and mortality (Khemani and Mehdirad, 2020). Endothelial dysfunction is common in patients with ME/CFS and is associated with severity of symptoms and immune response (Scherbakov et al., 2020). Heart rate variability (HRV) is widely used as a standard method of measuring autonomic dysfunction in cardiovascular and neurological disorders (Rajendra Acharya et al., 2006).

Hyperbaric oxygen (HBO2) (PO2 240–280kPa) delivered by inhalation in a hyperbaric chamber in daily treatments over several weeks, has several anti-inflammatory effects. Hyperbaric

Trial Code: HOT-LOCO  
Version No: v.4  
Date: 2022-01-03  
EudraCT No: 2021-000764-30

Oxygen Therapy/Treatment (HBOT) has been used safely for a century to treat other chronic inflammatory conditions such as radiation cystitis (Oscarsson et al., 2019), fibromyalgia (Efrati et al., 2015) and acute inflammatory conditions such as ulcerative colitis (Dulai et al., 2020). HBOT has shown beneficial effects on endothelial function in patients with slow coronary flow (Li et al., 2018). Usefully, it is possible to perform a placebo-controlled double-blind trial with HBO2 (Lansdorp and van Hulst, 2018).

HBO2 has been used off-label as one of few potentially curative treatments for acute COVID-19. Case series and a case control-study using HBO2 have shown faster recovery and reduced need for ICU treatment (Guo et al., 2020, Thibodeaux et al., 2020, Gorenstein et al., 2020). RCTs are ongoing, including one at the Karolinska University Hospital (Clinicaltrials.gov identifier: NCT04327505). Multiple hypotheses have been proposed for the effect of the therapy, with the common denominator being normalization of hypoxic- and inflammatory response (De Maio and Hightower, 2020, Kjellberg et al., 2020, Paganini et al., 2021).

One of the most studied effects of HBO2 is attributed to Hypoxia Inducible Factor-1 (HIF-1) and target genes (Thom, 2011). One target for HIF-1 regulation, which is known to be associated with COVID-19, is Angiotensin Converting Enzyme 2 (ACE2). Hospitalized patients with COVID-19 have a three-fold higher expression of ACE2 in the lungs compared to healthy controls (Chua et al., 2020), suggesting a susceptibility for severe infection or an adaptive response. HIF-1 has been shown to suppress ACE2, making HIF-1 modulation an interesting therapeutic target in COVID-19 (Serebrovska et al., 2020). Agents that stabilize HIF-1 have been proposed for COVID-19 (Afsar et al., 2020). A major challenge in translating HIF-regulation into clinical practice is the complex adaptation to hypoxia and the intricate interplay between three different HIFs. The crosstalk between hypoxia and inflammatory pathways adds further complexity to the system (D'Ignazio et al., 2016).

## 2.2 Research hypothesis

- HBO2 can induce HIF signalling independent of heart, lung and brain function, thus has the potential to reduce inflammation, restore normal hypoxic response and thereby reduce morbidity in Long COVID.
- HBO2 is safe and tolerable for Long COVID patients and the effect is associated with relief in symptoms and thereby improve HRQoL.
- The effect can be monitored by markers of oxidative stress in blood and by non invasive assessment of endothelial dysfunction and autonomic dysfunction.
- Treatment results are not transient and thereby also cost efficient.
- The effect is related to regulation of hypoxia and inflammatory pathways.

|             |                |
|-------------|----------------|
| Trial Code: | HOT-LOCO       |
| Version No: | v.4            |
| Date:       | 2022-01-03     |
| EudraCT No: | 2021-000764-30 |

## 2.3 Rationale for conducting the trial

Long COVID seems to affect approximately 10% of people infected with SARS-CoV-2, most of them are young women (Sivan and Taylor, 2020). To date, few treatment options are available. With over 100 million confirmed COVID-19 cases globally (600 000 in Sweden), the healthcare systems and their infrastructure are at risk of collapse if we cannot find an effective way of treating these patients. Karolinska University Hospitals was one of the first centers in the world to set up a multidisciplinary clinic for post covid sequelae and is now being overwhelmed with referrals of suspected Long COVID.

The most common symptoms in Long COVID is chronic fatigue and autonomic dysregulation that are also hallmarks of Fibromyalgia (Sarzi-Puttini et al., 2020) and Myalgic Encephalomyelitis/Chronic Fatigue Syndrome (ME/CFS) (Lim et al., 2020) and some patients are also diagnosed with Postural Orthostatic Tachycardia Syndrome (POTS) and they may all be different semblance of the same chronic inflammatory disease. HBOT has been shown to have positive effect on ME/CFS and fibromyalgia in small clinical trials (Efrati et al., 2015, Yildiz et al., 2004, Akarsu et al., 2013).

If HBO2 is effective for relieving symptoms in Long COVID there would be an obvious benefit for the individual patient. There is also a potential significant health-economic benefit if there is a lasting effect. The multiple explanatory endpoints may add valuable information about the disease for future interventional trials even with a negative result on the primary endpoint.

## 3. Benefit-risk evaluation

### 3.1 The risk group

There is currently no effective treatment available for Long COVID and since this is a new disease, there remain uncertainties regarding diagnosis, prognosis and mechanisms of action. There is emerging evidence that this may be an enormous problem for individuals, health-care and society. Diagnosis of Long COVID is mainly a clinical definition based on symptoms and it is difficult to find objective measurements. Patients that have been suffering from Long COVID since the first wave have often been misunderstood by the health care society and are desperate to find a cure for the disease. HBO2 has the theoretical potential to reverse or reduce symptoms in Long COVID. The nature of the disease, which provokes multiple symptoms and a low quality of life make the risk group a 'vulnerable group' and it is important to make sure that the subjects are not unduly influenced by the expectation or benefits associated with participation. Therefore, we will conduct a placebo-controlled, double-blind, clinical trial in compliance with Good Clinical Practice (GCP), the Declaration of Helsinki and national regulatory requirements. The written information has a neutral language explaining both risks and potential benefits and the investigators are instructed to keep a neutral tone when delivering oral information. The cause of Long COVID is still not known and optimal

|             |                |
|-------------|----------------|
| Trial Code: | HOT-LOCO       |
| Version No: | v.4            |
| Date:       | 2022-01-03     |
| EudraCT No: | 2021-000764-30 |

management is far from defined. We present a plausible hypothesis of the mechanism and a possible cure. Since there are no better options than 'expectation', and HBOT has been safely and effectively used in other chronic inflammatory conditions, the potential benefit for the subjects outweigh the risk.

## 3.2 General risks with HBO2

HBOT is a well-established method that has been used for almost a century for several different indications. The mechanisms for its efficacy are not fully understood but it is generally regarded as safe, with few adverse events; serious adverse events are extremely rare. The Undersea and Hyperbaric Medical Society (UHMS) have reported a total of 40 complications per 10,000 treatments during 463,293 treatments over two years (Moon, 2019). Adverse events per 10,000 treatments include: ear pain 20, confinement anxiety 8, hypoglycaemic event 5, shortness of breath 2, oxygen-induced seizure 2, sinus pain, 1, chest pain. HBOT has very few contraindications that are all relative to the treatment environment; they include claustrophobia, medical history of spontaneous pneumothorax, severe COPD, and pregnancy.

